### 4.2 Exclusion Criteria

- Leukaemic transformation ( $>20\%$  blasts in blood, marrow or extramedullary site).
- Accelerated phase of disease as indicated by  $\geq 10\%$  blasts in the peripheral blood
- Treatment of ET, PV or MF with Interferon alpha or other investigational agents for their MPN within 6 months prior to trial entry. JAK inhibitors, such as ruxolitinib, are allowed if taken continuously for  $\geq 6$  months prior to registration (dose changes during that period will be allowed)
- Any of the following previous thrombotic events at any time:
  - Portal or other splanchnic venous thrombosis
  - Vascular access complication
  - Ischemia cerebrovascular
  - Stroke
  - Transient Ischaemic attack
  - Superficial thrombophlebitis
  - Venous Thromboembolic events including pulmonary embolism (PE) and deep vein thrombosis (DVT)
  - Peripheral vascular ischemia
  - Visceral arterial ischemia
  - Acute coronary syndrome
  - Myocardial infarction

- Previous malignancy within 5 years with the exception of adequately treated cervical carcinoma in situ or localized non-melanoma skin cancer
- Previous endometrial cancer, hyperplasia or polyps
- Prior treatment with hematopoietic stem cell transplantation
- Patients who do not carry JAK-2V617F, CALR 5bp insertion (exon 9) or CALR 52bp deletion (exon 9) mutations, or whose allele burden is <20% at study entry (**assessed via central review**)
- Female patients receiving hormone replacement therapy
- Hypertriglyceridemia > grade 1
- Any serious underlying medical condition (at the judgment of the Investigator), which could impair the ability of the patient to participate in the trial (e.g. liver disease, active autoimmune disease, uncontrolled diabetes, uncontrolled infection (HIV, Hepatitis B and C), known genetic defect (apart from MPN) relating to venous thromboembolic events, or psychiatric disorder precluding understanding of trial information)
- Known hypersensitivity to tamoxifen or hypersensitivity to any other component of tamoxifen
- Concomitant drugs contraindicated for use with the trial drug according to the Summary of Product Characteristics (Appendix 8)
- Known planned scheduled elective surgery during study with the exception of dental and low risk eye surgery (e.g. cataracts)

## 5. SCREENING AND CONSENT

### 5.1 Screening

Investigators will be expected to maintain a Screening Log of all potential study candidates. This Log will include limited information about the potential candidate (e.g. date of birth and gender), the date and outcome of the screening process (e.g. enrolled into study, reason for ineligibility, or refused to participate).

For patients who appear to meet the criteria for participation in the study, the Investigator will provide information to allow them to make an informed decision regarding their participation. If informed consent is given (see section 5.2), the Investigator will conduct a full screening evaluation to ensure that the patient satisfies all inclusion and exclusion criteria. A patient who gives written informed consent and who satisfies all the inclusion and exclusion criteria may be registered onto the study. Note that assessments conducted as standard of care do not require informed consent and may be provided as screening data if conducted within the stipulated number of weeks prior to registration. Assessments required in screening are listed in the schedule of assessments and below.

#### 5.1.1 Screening Assessments

All patients will be screened prior to registration. The following screening assessments will be performed within 6 weeks prior to trial entry unless stated otherwise (see section 7.2 for more detail):

- Collect demographic data
- Collect medical history (including prior diagnosis and treatments) with particular attention to gynaecological history
- Medical exam including height (baseline only), weight, blood pressure, WHO performance status, palpation of liver and spleen
- Ultrasound to assess spleen size
- Patient to complete MPN-SAF (Appendix 9)

#### Blood tests

- Full blood count and biochemistry – please see section 7.2 for full details of tests to include
- Full fasting lipid profile to include triglycerides
- Blood sample collection for **central analysis** of JAK2-V617F, CALR 5bp insertion (exon 9) and CALR 52bp deletion (exon 9) mutant allele burden. Patients must be able to start trial treatment within 6 weeks of this blood sample collection and patients cannot be registered until confirmation of eligibility has been received from the Trials Office that the patient has an allele burden ≥20%.

## 5.2 Informed Consent

It is the responsibility of the Investigator, as captured on the Site Signature and Delegation Log, to obtain written informed consent for each patient prior to performing any trial related procedure. A Patient Information Sheet is provided to facilitate this process. Investigators must ensure that they adequately explain the aim, trial treatment, anticipated benefits and potential hazards of taking part in the trial to the patient. The Investigator should also stress that the patient is completely free to refuse to take part or withdraw from the trial at any time. The patient should be given ample time (e.g. 24 hours) to read the Patient Information Sheet and to discuss their participation with others outside of the site research team. The patient must be given an opportunity to ask questions which should be answered to their satisfaction. The right of the patient to refuse to participate in the trial without giving a reason must be respected.

If the patient expresses an interest in participating in the trial they should be asked to sign and date the latest version of the Informed Consent Form. The Investigator or designate must then sign and date the form. A copy of the Informed Consent Form should be given to the patient, a copy should be filed in the hospital notes, and the original placed in the Investigator Site File (ISF). Once the patient is entered into the trial the patient's trial number should be entered on the Informed Consent Form maintained in the ISF. In addition, if the patient has given explicit consent a copy of the signed Informed Consent Form must be sent in the post to the Trials Office for review.

Details of the informed consent discussions should be recorded in the patient's medical notes, this should include date of, and information regarding, the initial discussion, the date consent was given, with the name of the trial and the version number of the Patient Information Sheet and Informed Consent Form. Throughout the trial the patient should have the opportunity to ask questions about the trial and any new information that may be relevant to the patient's continued participation should be shared with them in a timely manner. On occasion it may be necessary to re-consent the patient in which case the process above should be followed and the patient's right to withdraw from the trial respected. The patient should be given ample time to read changes made to the patient information sheet, which may vary depending on the nature of the change and may re-consent at the same visit that new information is provided, if they wish to do so.

Electronic copies of the Patient Information Sheet and Informed Consent Form are available from the Trials Office and should be printed or photocopied onto the headed paper of the local institution.

Details of all patients approached about the trial should be recorded on the Patient Screening/Enrolment Log and with the patient's prior consent their General Practitioner (GP) should also be informed that they are taking part in the trial. A GP Letter is provided electronically for this purpose.

## 6. TRIAL ENTRY

Patients will be registered to the trial via the Cancer Research UK Clinical Trials Unit (CRCTU). Confirmation that the patient meets the inclusion criteria ( $\geq 20\%$ ) for peripheral blood mutant allele burden must have been confirmed by the Trials Office prior to registration.

Registration can be conducted via the eCRF by logging on to:

**<https://www.cancertrials.bham.ac.uk/TAMARINLive>**

Or calling ☎: **[name] or [name]; 9am-5pm Monday to Friday.**

Login details will be provided by the Trials Office as part of site initiation.

An eligibility checklist and registration form (found in the ISF) should be completed prior to registration (via phone) by the Investigator or designee. If the patient is registered via the online system, the eligibility checklist should be completed prior to registration and following registration, the patient trial number will be provided and a report can be printed as a confirmation. If the patient is registered via phone, the patient trial number will be given over the telephone, followed by a fax confirmation.

## 7. TREATMENT DETAILS

### 7.1 Trial Treatment

Tamoxifen is considered an investigational medicinal product (IMP) for the purposes of the trial from the point of dispensing.

Sites are to use tamoxifen from standard hospital stock. No free or discounted product is offered as part of the trial.

Any brand of tamoxifen may be used provided it is in tablet form and administered orally.

Medication labels in English will be provided in the Pharmacy File. These must be added at the point of dispensing and the local information and patient trial number added.

Patients should be given enough tamoxifen to last until their next scheduled visit but the schedule for prescribing is at local site discretion (e.g. can be prescribed 4 weekly initially, rather than 2 weekly).

Patients will receive 20mg once daily. Patients should start trial treatment following registration but this must be within 6 weeks of the assessment of allele burden and continue daily for 24 weeks. At this point, further treatment may be prescribed if the patient is receiving benefit (at the discretion of the treating Investigator).

As guidance, treatment continuation will be encouraged but not mandated for patients who do not experience persistent side effects greater than grade 1 or thrombotic events of any grade and that fulfil one or more of the following criteria at 24 weeks:

- $\geq 25\%$  reduction in allele burden compared to baseline
- Improvement of haematological response compared to baseline without changes in cytoreductive therapy dose according to 2009 ELN criteria for ET/PV patients and to IWG-MRT response criteria for MF patients
- A decrease in requirement for cytoreduction without deterioration of haematological response compared to baseline according to 2009 ELN criteria for ET/PV patients and to IWG-MRT response criteria for MF patients

### 7.2 Assessments

#### 7.2.1 Demographic data and medical history

A medical history and the patient's demographics will be taken within 6 weeks of registration including the following:

- Age
- Sex
- Disease type
- JAK2-V617F, CALR 5bp insertion and CALR 52bp deletion status (if known)
- Previous medical conditions (especially gynaecological)
- Previous treatments

#### 7.2.2 Medical examination/symptom assessment

A physical examination and symptom assessment will be assessed within 6 weeks prior to registration, at weeks 4, 12, 18, 24 and 28 days following treatment discontinuation and will include:

- WHO performance status
- Blood pressure
- Palpation of liver and spleen
- Weight

The medical examinations should also be targeted around any AEs experienced. The week 18 assessment may be performed via telephone should this be more convenient for the patient and a medical examination and haematology and biochemistry assessments are not required. This should focus on escalation or de-escalation in Tamoxifen dose, Adverse Events, Serious Adverse Events, thrombotic events, etc. However, the patient should attend this visit should there be a need for a dose escalation or de-escalation as this should be reviewed and implemented at week 18. Patients continuing with trial treatment beyond 24 weeks will receive a medical exam every 12 weeks or more frequently at local Investigator discretion.

#### 7.2.3 Ultrasound

An ultrasound to assess spleen size will be performed within 6 weeks prior to registration and repeated at 24 weeks. For PV/ET patients entering the trial with PR and enlarged spleen, the

ultrasound at 24 weeks will be performed earlier if a CR is suspected. Thus all patients will have 2 ultrasounds in total. Paper copies of ultrasound results should be posted to the Trial Office upon receipt.

#### 7.2.4 Haematology

A full blood count will be performed within 6 weeks prior to registration, at weeks 4, 12, 18, 24 and 28 days following treatment discontinuation and will include:

- Red blood cell (RBC count)
- Haemoglobin (Hb)
- White blood cell (WBC) count
- Lymphocytes
- Platelets
- Haematocrit (Hct)
- Absolute neutrophil count (ANC)
- Blood film

Patients continuing with trial treatment beyond 24 weeks will receive a full blood count every 12 weeks or more frequently at local investigator discretion.

#### 7.2.5 Biochemistry

Standard biochemistry tests will be performed within 6 weeks prior to registration, at weeks 4, 12, 18, 24 and 28 days following treatment discontinuation and must include the following tests:

- Alanine Aminotransferase (ALT) or Aspartate Aminotransferase (AST)
- Lactate dehydrogenase (LDH)
- Bilirubin
- Estimated glomerular filtration rate (eGFR) or calculated creatinine clearance
- Alkaline Phosphatase (ALP)
- Calcium

Patients continuing with trial treatment beyond 24 weeks will receive biochemistry tests every 12 weeks or more frequently at local investigator discretion.

#### 7.2.6 Lipid profile

As tamoxifen is commonly associated with elevated triglyceride levels, a full fasting lipid profile to include triglycerides will be performed at baseline, 12 weeks and 24 weeks. If triglycerides are elevated at 24 weeks and the patient is continuing therapy with tamoxifen, these levels should continue to be monitored at local clinical discretion.

#### 7.2.7 Bone marrow evaluation

Patients will be required to undergo a bone marrow aspirate and trephine biopsy 24 weeks after starting treatment with tamoxifen. This will be assessed centrally for response using IWG-MRT Criteria (Appendix 6) for MF patients and 2013 ELN Criteria (Appendix 7) for ET/PV patients.

#### 7.2.8 Quality of Life

All patients will be required to complete the Myeloproliferative Neoplasm Symptom Assessment Form Total Symptom Score (MPN-SAF TSS) [23] at baseline and week 24 of the study. The questionnaire can be found in Appendix 9. This will be used in order to assess symptom improvement which forms part of the response evaluation. The research team should complete the first page of the booklet prior to providing this to the patient.

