## 1.2 Trial Rationale

### 1.2.1 Justification for patient population

This trial will be open to all patients with MPN who have a measureable disease burden (defined by quantifiable abnormal clone of  $\geq 20\%$  mutated JAK2-V617F, CALR 5bp insertion (exon 9) or CALR 52bp deletion (exon 9)).

The eligibility criteria have also been carefully considered to take into account the well-established safety profile of tamoxifen and the trial is therefore open only to males and post-menopausal women.

Patients with a prior thrombosis will also be excluded as both tamoxifen and MPN are associated with a higher risk of thrombosis. To try and ensure patients have stable blood counts whilst on trial, and again minimise the risk of thrombosis, patients will also be able to continue with existing therapy for their MPN such as hydroxycarbamide, venesection, and aspirin. However, patients will not be able to continue/receive concomitant treatment with therapies that lower the allele burden such as interferon alpha) as this would prevent accurate assessment of the primary outcome. JAK inhibitors, such as ruxolitinib, will be allowed if taken continuously for  $\geq 6$  months prior to registration, as any changes in allele burden are expected to occur early during treatment.

In addition, only patients whose disease is currently well controlled on standard therapies will be eligible which will further minimise the risk of thrombosis.

Another well described side effect of tamoxifen is women experiencing symptoms of premature menopause and uterine changes. This study will therefore only include post-menopausal women.

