#### 7.2.9 Assessment of response

##### Weeks 2-16

ET and PV patients will be assessed at each protocol scheduled visit for haematological response according to 2009 ELN criteria [1] (Appendix 5) by the Investigator. This will include review of the platelet count, HCT (PV only) and WBC in combination with ultrasound (if applicable) and requirement for venesection. An ultrasound is only applicable prior to 24 weeks if the patient entered the trial in haematological PR with an enlarged spleen on imaging. In these cases, an ultrasound showing a normal spleen must be obtained in order to report haematological CR when this is suspected.

For MF patients, assessment of haematological response will be performed at each protocol scheduled visit using the IWG-MRT criteria [2] (Appendix 6). "Maintenance of response" will be defined as no evidence of disease progression. Disease progression is defined in Appendix 6 but please note a bone marrow to confirm disease progression prior to 24 weeks should only be performed if clinically indicated according to local practice.

---

### Week 24

The trial bone marrow performed at week 24 will be centrally reviewed and a trephine histopathology report issued. Sites will be requested to provide an anonymised report from the latest bone marrow assessment available for each patient prior to registration to ensure a comparison report can be prepared from the trial biopsy at 24 weeks.

Central review of the bone marrow trephine sample will not be fed back in real time and therefore cannot be a guide for patient management.

Sites will then perform the 24 week response assessment upon receipt of this histopathology report using all the relevant clinical data.

For ET and PV patients, assessment of response at 24 weeks will be performed against the 2013 ELN criteria [3] (Appendix 7) using the BM report and results of blood counts (platelets, WBC, haematocrit), blood film, liver/spleen on palpation, symptom assessment (via MPN SAF) and occurrence of haemorrhagic or thrombotic events.

For MF patients, assessment of response at 24 weeks will be performed against IWG-MRT criteria [2] (Appendix 6) using the BM report and results of blood counts (haemoglobin, neutrophils, platelets), blood film for presence of immature myeloid cells and spleen on palpation.

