## APPENDIX 6 – REVISED RESPONSE CRITERIA FOR MYELOFIBROSIS

Ref: Tefferi *et al.* (2013). Revised response criteria for myelofibrosis: International Working Group-Myeloproliferative Neoplasms Research and Treatment (IWG-MRT) and European LeukemiaNet (ELN) consensus report. Blood **122** (8) 1395-1398 [2].

These criteria will be used to assess the endpoints of maintenance of response (no evidence of disease progression) in patients with MF and response assessment at 24 weeks.

| Response categories                                                               | Required criteria (for all response categories, benefit must last for ≥12 wk to qualify as a response)                                                                                                                                                                                                                                                                                                                                                                                                                                                                                                                                                                           |
|-----------------------------------------------------------------------------------|----------------------------------------------------------------------------------------------------------------------------------------------------------------------------------------------------------------------------------------------------------------------------------------------------------------------------------------------------------------------------------------------------------------------------------------------------------------------------------------------------------------------------------------------------------------------------------------------------------------------------------------------------------------------------------|

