§See above for definitions of anemia response, spleen response, and progressive disease. Increase in severity of anemia constitutes the occurrence of new transfusion dependency or a  $\geq 20$  g/L decrease in hemoglobin level from pretreatment baseline that lasts for at least 12 weeks. Increase in severity of thrombocytopenia or neutropenia is defined as a 2-grade decline, from pretreatment baseline, in platelet count or absolute neutrophil count, according to the Common Terminology Criteria for Adverse Events (CTCAE) version 4.0. In addition, assignment to CI requires a minimum platelet count of  $\geq 25,000 \times 10^9/L$  and absolute neutrophil count of  $\geq 0.5 \times 10^9/L$ .

||Applicable only to patients with baseline hemoglobin of  $< 100$  g/L. In patients not meeting the strict criteria for transfusion dependency at the time of study enrollment (see as follows), but have received transfusions within the previous month, the pretransfusion hemoglobin level should be used as the baseline.

¶Transfusion dependency before study enrollment is defined as transfusions of at least 6 units of packed red blood cells (PRBC), in the 12 weeks prior to study enrollment, for a hemoglobin level of  $< 85$  g/L, in the absence of bleeding or treatment-induced anemia. In addition, the most recent transfusion episode must have occurred in the 28 days prior to study enrollment. Response in transfusion-dependent patients requires absence of any PRBC transfusions during any consecutive "rolling" 12-week interval during the treatment phase, capped by a hemoglobin level of  $\geq 85$  g/L.

#In splenectomized patients, palpable hepatomegaly is substituted with the same measurement strategy.

\*\*Spleen or liver responses must be confirmed by imaging studies where a  $\geq 35\%$  reduction in spleen volume, as assessed by MRI or CT, is required. Furthermore, a  $\geq 35\%$  volume reduction in the spleen or liver, by MRI or CT, constitutes a response regardless of what is reported with physical examination.

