| Complete Remission                                                                                                                                                                                                                                                                                                                                                                                                                                                                                                                                                                                                                                                                                                                                              |                                                                                                                                                                                     |
| A                                                                                                                                                                                                                                                                                                                                                                                                                                                                                                                                                                                                                                                                                                                                                                      | Durable* resolution of disease-related signs including palpable hepatosplenomegaly, large symptoms improvement,† AND                                                                |

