| 
Molecular response is not required for assignment as complete response or partial response. Molecular response evaluation requires analysis in peripheral blood granulocytes. Complete response is defined as eradication of a pre-existing abnormality. Partial response applies only to patients with at least 20% mutant allele burden at baseline. Partial response is defined as <math>\geq 50\%</math> decrease in allele burden.
 
WBC, white blood cell.
 
*Lasting at least 12 wk.
 
†Large symptom improvement (<math>\geq 10</math>-point decrease) in MPN-SAF TSS.
 
‡For the diagnosis of post-PV myelofibrosis, see the IWG-MRT criteria; for the diagnosis of myelodysplastic syndrome and acute leukemia, see WHO criteria.
 |                                                                                                                                                                                     |

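### Some week-24 responder categories cannot be assigned as written: symptoms are scored only at baseline and week 24, and the platelet floor for MF Clinical Improvement is impossible

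*Combined protocol and SAP*

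**What the plan says.** The proportion of patients in each response category at 24 weeks is a secondary outcome (sections 2.2 and 12.1.2). It uses the IWG-MRT criteria for MF (Appendix 6) and the 2013 ELN criteria for ET/PV (Appendix 7). Section 12.2.2 reports it descriptively, as numbers and percentages.

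- **Symptom score.** Section 7.2.8 requires the "Symptom Assessment Form Total Symptom Score (MPN-SAF TSS) [23] at baseline and week 24 of the study" and gives its purpose: "This will be used in order to assess symptom improvement which forms part of the response evaluation". The schedule of events agrees. The row has no entry at weeks 4, 12 or 18, beyond week 24, or at the end-of-study visit.
- **MF.** The header of the Appendix 6 table states that "for all response categories, benefit must last for ≥12 wk to qualify as a response". CI can be reached through an anaemia, spleen or symptoms response, and the symptoms response is a fall of at least 50% in TSS. A footnote makes CI conditional on a platelet count of at least 25,000 x 10^9/L.
- **ET/PV.** In Appendix 7, criterion A for CR reads "Durable* resolution of disease-related signs including palpable hepatosplenomegaly, large symptoms improvement", with near-identical wording for PR. The asterisk means "Lasting at least 12 wk". The symptom phrase has its own dagger footnote: a fall of at least 10 points in TSS, with no duration given.

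**The concern.** A requirement that a benefit last 12 weeks needs evidence at two times at least 12 weeks apart. The plan takes the symptom score once after baseline. If the criteria are applied as printed, a patient whose symptoms improved early and stayed better cannot be credited, and the platelet floor would close CI to MF patients by every route.

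Sites assign the week-24 categories themselves (section 7.2.9), across 13 to 15 centres. Some may apply the text literally, some may waive the 12-week rule for symptoms, and some may silently correct the platelet figure. The reported proportions would then partly reflect how each centre filled the gaps. For MF this reaches a second secondary outcome, improvement in response category, which also uses the Appendix 6 categories.

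**Working it through.** **The plan's own figure.** The documents give no expected rate for this outcome. The design figure in section 12.6 reproduces with exact binomial tails: with n = 42 and activity declared at 3 or more responders, P(X >= 3 | p = 0.02) = 0.0515, within the one-sided 0.10, and P(X >= 3 | p = 0.10) = 0.8049, meeting 80%. It rests on allele burden alone, so nothing below changes it.

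**Step 1: can 12-week durability of the symptom score be shown?** Count pairs of post-baseline assessments at least 12 weeks apart.

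| Assessment | Post-baseline weeks | Pairs at least 12 weeks apart |
|---|---|---|
| TSS as planned | 24 | 0 |
| TSS with week 12 added | 12, 24 | 1 (24 - 12 = 12) |
| Blood counts as planned | 4, 12, 18, 24 | 3 (18 - 4 = 14; 24 - 4 = 20; 24 - 12 = 12) |

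The week-24 form cannot stand in for an earlier score. In Appendix 9 the fatigue item and the stem for the other symptoms ask about the past 24 hours; only the weight-loss item looks back further, over six months.

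**Step 2: MF.** The 12-week rule is explicit for all response categories and the symptoms response is defined by TSS. With 0 qualifying pairs, that route to CI cannot be met at week 24. The anaemia and spleen routes, progressive disease and stable disease do not depend on serial TSS. CR and PR ask for resolution of symptoms without a TSS cut-off.

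**Step 3: ET/PV.** Criterion A can be read in two ways.

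| Reading of the asterisk | TSS evidence needed | Available as planned? |
|---|---|---|
| Covers signs and symptom improvement | Two post-baseline scores at least 12 weeks apart | No; CR and PR cannot be assigned |
| Covers signs only | Baseline and week 24 | Yes |

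The protocol does not say which applies.

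**Step 4: the platelet floor**, all in units of 10^9/L.

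- Against the lower limit for MF CR (100): 25,000 / 100 = 250 times.
- Against the lower limit in the second PR definition (50): 25,000 / 50 = 500 times.
- Against the PV/ET entry ceiling in section 4.1 (600): 25,000 / 600 = about 42 times.

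The same appendix also requires platelets below the upper normal limit for CR and PR. The pattern fits a unit mix-up, since 25,000 per microlitre x 10^6 microlitres per litre = 25 x 10^9/L. The documents cannot show whether it arose here or in the cited criteria.

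**Step 5: how many patients.** The recruitment aims are at least 15 PV, 10 ET and 5 MF among 42. If the aims are met, MF patients number between 5 and 42 - 15 - 10 = 17. One MF patient placed differently moves the MF category percentages by 1/5 = 20 points at the lower end and 1/17 = about 6 points at the upper. These figures show sensitivity; they do not count patients whose category would change.

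**The case against.** The strongest reply is that little is truly unassignable. Progressive disease, MF stable disease, and no response in a patient who fails another criterion need no serial TSS. Section 7.2.2 provides an unscored symptom assessment at weeks 4, 12, 18 and 24, which might support symptom resolution for MF CR and PR. In Appendix 7 the asterisk sits on the resolution of signs, while symptom improvement has a separate footnote without a duration. The platelet figure is an obvious slip that no assessor would apply. The outcome is descriptive, with no decision attached.

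Most of this stands and limits the point to the responder categories named above. It does not reach the MF symptoms response, which is defined by TSS and carries an explicit 12-week rule. Nor does it settle the ET/PV reading, and relying on assessors to correct a printed threshold leaves the correction to each centre.

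Two further criticisms might be inferred from the text, and neither is well supported.

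- **Low baseline scores.** A patient with a baseline TSS below 10 cannot fall by 10 points, and the protocol says that "only patients whose disease is currently well controlled on standard therapies will be eligible". But the 10-point threshold belongs to the adopted consensus criteria, eligibility defines control in ET/PV by counts and venesections rather than symptoms, and the share of such patients is not given.
- **The MF input list.** The week-24 list in section 7.2.9 ends with "blood film for presence of immature myeloid cells and spleen on palpation" and names neither symptoms nor liver. The same section tells sites to use all relevant clinical data and to assess against the full IWG-MRT criteria, and both items are collected.

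**Conclusion.** The point holds in a limited form.

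- **MF, symptoms route to CI:** it cannot be met at week 24 under the planned schedule. This needs no assumption beyond the text of Appendix 6 and section 7.2.8.
- **ET/PV CR and PR:** unassignable only if the 12-week mark covers symptom improvement. A reader might infer that the ET/PV response rate must be 0% whatever the drug does. The documents do not support that without this condition, because the signs-only reading is equally open and needs only the two planned scores.
- **MF CI platelet floor:** 250 times the CR lower limit in the same appendix. Read literally, no patient can be CI by any route. It is very probably a unit error.

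The effect falls on a descriptive secondary outcome and, for MF, on improvement in response category. The ET/PV improvement outcome uses the 2009 criteria in Appendix 5, which contain no TSS, and is unaffected, as are the primary endpoint, the sample size of 42 and the 3-responder rule.

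**What to change.** 1. Add the self-completed MPN-SAF TSS to the existing week-12 visit (section 7.2.8 and the schedule of events). Count improvement present at both weeks 12 and 24 as durable. The gap is exactly 12 weeks, so say that nominal visit weeks are used.
2. Report patients without a week-12 score, or who first improve after week 12, as durability not assessable, separately from non-responders.
3. State in section 7.2.9 or Appendix 7 whether the 12-week rule applies to the ET/PV symptom item.
4. Reconcile the CI platelet threshold with the other platelet figures in Appendix 6 and with the cited criteria.

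Optional: tabulate ET/PV patients with baseline TSS below 10 separately, and name symptoms and liver palpation in the MF week-24 list.

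The cost is one extra questionnaire at a visit already attended, plus wording. The remedy is partial: durability stays unassessable for patients already past week 12 and for late improvers, including any who improve only after the week-18 dose review.
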